### The early childhood education and development (ECED) program

The overarching objective of the program is to improve poor children’s overall development and readiness for further education within a sustainable quality ECED system. To achieve this objective, the project aims to:

1) Increase the capacity of poor communities to engage in participatory planning that will result in new or improved ECED services for their children and families.

2) Prepare the foundation for a sustainable ECED system through budgetary commitments from participating districts, establishment of a national quality assurance and professional development system, and district capacity building.

3) Ensure continuous improvement of service delivery and system building through establishing effective project management, and monitoring and evaluation.

The project targets an estimated 738,000 children aged 0 to 6 years and their parents/caretakers living in approximately 6,000 poor communities located in 3,000 villages within 50 poor districts throughout Indonesia. Particular attention was to be given to children aged 2 to 4 years as some children may enroll in kindergarten by the age of 5 years. The project is additionally expected to have a demonstration effect on the Government, which may then expand the coverage of ECED services for poor children in Indonesia [28].

This project, implemented from 2006 to 2012, is financed through a credit from International Development Assistance by the World Bank and a grant from the Government of the Kingdom of the Netherlands. Such a loan is particularly applicable to the ECED sector in Indonesia given that it is at the ‘start-up stage of developing a system and that it requires major technical inputs’ [28]. The project costs a total of US$127.7 million (International Development Association funding from the World Bank equaling US$67.5 million, the Netherlands grant equaling US$25.3 million and the Government of Indonesia US$34.9 million).

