##### Study hypotheses

The overarching goal of the ECED program is to improve poor children’s overall development and readiness for further education within a sustainable quality ECED system. However, for the purposes of the trial we required more specific aims and thus developed the following hypotheses. Relative to the non-intervention group, participants in the experimental group of the study will:

1) Have greater access to ECED services.

2) Have a higher participation rate in ECED services.

3) Have a higher enrolment rate in school at earlier ages.

4) Be more ‘school ready’.

5) Have higher community awareness about the importance of ECED.

6) Have higher persistent breastfeeding rates, improved nutrition and improved early childhood stimulation.

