### Planned analyses

As noted above, there are several hypotheses under the trial. One of the risks when collecting a large set of outcome variables is to highlight false positives in the final analysis, that is, significant coefficients are identified in the final analysis when, in fact, these could be due to natural randomness. To reduce this risk, for each hypothesis below we list (in bullets) which outcome variables we will use to test our research hypotheses. We believe that by limiting the analyses to a parsimonious set of variables defined *ex ante*, the risk of false positives is greatly reduced. The hypotheses under the trial are whether the ECED program has led to:

1) Greater access to ECED services

• The number of children aged 0 to 6 years in the village/ECED centers in the village

2) Higher participation rate in ECED services

• The fraction of children that attend an ECED service at least once a week by age five years

3) Higher enrolment rate in school at earlier ages

• The fraction of children aged 6 to 8 years that enrolled in primary school at the age of 6 years. (For children aged 7 and 8 years, their age of enrolment will be inferred by the grade they are in at the time of the survey)

4) More ‘school ready’ children

• The summary values of the EDI in the domains of physical health and well-being, social competence, emotional maturity, language and cognitive skills, communication skills, and general knowledge

• Mean score on the SDQ in the areas of emotional symptoms, conduct problems, hyperactivity/inattention, peer relationship problems and pro-social behavior

• The average numbers of stages children pass on the DCCS task (there are three stages)

• The fraction of tasks children can perform in the areas of gross motor skills, fine motor skills, language skills, cognitive skills and socio-emotional skills

5) Higher community awareness about the importance of ECED

• Parental knowledge about the location of key ECED services in the village

6) Higher persistent breastfeeding rates, improved nutrition and improved early childhood stimulation.

• Average number of months of exclusive breastfeeding for children when they were below the age of 6 months

• Height-for-age z-score, weight-for-height z-score

• Number of activities children engaged in last week (out of book reading, storytelling, drawing, music, playing with toys and helping in household chores) and fraction of children that play outside

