In addition to external validity, the other caution we have relates to the length of time between when the treatment and randomized control villages received the project. Most research literature to support the benefits of early intervention and child development are long-term studies that in many cases track into adulthood [2,41,42]. The current planned follow-up time for this study is more limited, and showing an impact might be difficult. Initially, the design called for 18 months between baseline and midline as well as 18 months difference in exposure to the project. Due to a combination of lack of adherence to the original study design and planned schedule, the time difference between baseline and midline data collection ended up being around 14 months, while the difference in exposure to the project between Batch 1 and Batch 3 was around 11 months by the time of the midline data collection. This short time span is precisely why the evaluation employed an additional matched control group. The advantage offered by the matched control group is that it allows us to track children who were not exposed to the project for the full 3 years. However, the primary disadvantage with the matched control group is the threat to internal validity.

While the project allowed for the provision of both center-based and outreach services for children, in practice most service provision has been center-based (based on World Bank operational data indicating that only 38% of the centers have organized outreach activities). The block grant was able to be used to equip the centers with toys, learning materials, food supplements and play equipment. The funding was also to be used to hire two local community members associated with each dusun, where one was to be trained as an ECED teacher and the other a community development worker to conduct outreach activities. The community was expected to provide infrastructure for the ECED center. The project funding to communities allows for flexibility in mechanisms of service provision, but stipulates that the services be targeted to children aged 0 through to 6 years with a specific focus on children aged 2 to 4 years, and poor families. This degree of flexibility at a community level means that there may be a large degree of variation across villages, also making it difficult to calculate dose and thus impact.

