In terms of the dose of ECED services, children in the study sample are likely to have differentiated exposure to the treatment. Our sampling strategy involved random recruitment of children from within two dusuns before it was known in which dusuns the new ECED services would be located. Children who reside in the two dusuns where the ECED project ended up being implemented are potentially more likely to benefit as they live closer to the ECED services. Additionally, children enrolled in the ECED service may also benefit more than a child living in the same dusun but not attending the ECED service. The distribution of benefits will depend on both the decisions of the household and the management of the ECED center. A household will decide to what extent to participate in outreach activities and to enlist their children in center-based activities. The management of the ECED center will decide on the mix of center-based and outreach activities, and if there is excess demand, selection of children into activities conducted at the ECED center (although in practice we have not observed selectivity even in the face of excess demand). The study questionnaires have been developed to collect as much information as possible to determine both attendance and frequency of attendance, but also reasons for participating (or not) in ECED services.

In conclusion this study has and will present some significant quality, analytical and methodological challenges. Many of these challenges are being addressed at present as the study team are designing the endline survey to be conducted in early 2013. Suggested strategies to help enhance our ability to draw conclusions from the study include increasing the duration of follow-up and collecting data for all children in the study villages through the schools rather than just following the sample cohort. Such strategies will be dependent on funding and support from the MoNE and the World Bank for ongoing commitment to the study.

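### Hypothesis 5 concerns awareness of how important ECED is, but its only listed outcome is whether parents know where services are, so a positive result would not support the stated conclusion

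*Protocol article*

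**What the plan says.** The Study hypotheses section states the fifth hypothesis for the experimental group as: "Have higher community awareness about the importance of ECED". Planned analyses repeats it as "Higher community awareness about the importance of ECED" and puts one bullet under it: "Parental knowledge about the location of key ECED services in the village".

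The bullets are not examples. The same section says that "for each hypothesis below we list (in bullets) which outcome variables we will use to test our research hypotheses", and it defends the short, pre-defined list as its protection against false positives. No variable listed under any of the six hypotheses records how important parents or the community consider ECED.

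On the intervention, the program's first aim is "participatory planning that will result in new or improved ECED services for their children and families", and the Discussion reports that "in practice most service provision has been center-based". Hypothesis 1 already measures supply, as the number of children aged 0 to 6 years per ECED center in the village.

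**The concern.** The hypothesis is about an attitude, and the variable is about geography. A parent can know where a center stands and give it no weight. Another can value early education highly in a village that has no center to point to. The variable also covers parents only, while the hypothesis speaks of the community.

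The intervention also acts directly on what is measured. Opening a center creates a location that can be known, whether or not anyone's view of ECED changes. A positive result could then be reported as a change in awareness when it partly repeats the supply result of hypothesis 1. A larger sample or better matching would not cure this, because the fault lies in what is measured.

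This is not a detail left to a statistical analysis plan. The article itself fixes the variable and presents the list as limiting.

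**Working it through.** The article gives no figure for this outcome, so there is nothing to reproduce. The check has three steps.

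**1. Construct against measure.** Hypothesis 5 names awareness of importance. Its one bullet names knowledge of location. The mismatch is visible on the page and needs no arithmetic.

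**2. Which comparison is exposed.**
- Endline, equation (1): Batch 1 against matched controls, which never receive the project. Any locations the project adds exist in one arm only.
- Midline, equation (3): Batch 1 at about 20 months against Batch 3 at about 9 months (Deviations from planned design and consequences for analysis). Both arms have project services, so the contrast in supply is smaller.

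**3. Can supply alone produce a positive result?** Write

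P(knows a location) = P(a service exists) × P(knows it, given that it exists)

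and hold the second factor equal in both arms, so that parents do not differ. This assumes that a parent with no service in the village counts as not knowing, which the article does not say. The presence and knowledge values are also assumed. From the sample size section come 10 children per village and an intracluster correlation (ICC) of 0.23. The design effect is 1 + 9 × 0.23 = 3.07, so 100 villages per arm give an effective 1,000 / 3.07 = 326 children per arm. Tests are two-sided at 0.05.

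| Knows if it exists | Presence, control v project | Measured knowledge | Gap (points) | Power |
|---|---|---|---|---|
| 50% | 50% v 60% | 25% v 30% | 5 | about 30% |
| 50% | 50% v 70% | 25% v 35% | 10 | about 80% |
| 50% | 50% v 90% | 25% v 45% | 20 | above 99% |
| 30% | 50% v 70% | 15% v 21% | 6 | about 51% |
| 70% | 50% v 70% | 35% v 49% | 14 | about 95% |

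With 90 villages per arm (the baseline sample has 90 matched controls), the second row falls to about 75%.

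The ICC of 0.23 comes from junior secondary enrolment and may be too low here, because presence is a village-level factor. In the second row the model implies a control-arm ICC of 0.5² × 0.5 × 0.5 / (0.25 × 0.75) = 0.33 and a project-arm ICC of 0.5² × 0.7 × 0.3 / (0.35 × 0.65) = 0.23. The standard error is then √[0.1875 × (1 + 9 × 0.333) / 1,000 + 0.2275 × (1 + 9 × 0.231) / 1,000] = 0.038. The 10-point gap is 2.63 standard errors, and power with 100 villages per arm is about 75%.

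A significant result for hypothesis 5 can therefore arise with no difference between parents. How likely that is depends on how many new locations the project adds, which the article does not report.

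**The case against.** The strongest reply is that the mechanism rests on definitions the article does not give. It does not say which services are key, or how a parent is scored where a service is absent. If knowledge is scored only among existing services, or if the key services are the midwife and the posyandu, most of the supply effect disappears. Outcome measures treats those two as often the commonest ECED services in a village. Grant rules also allow existing services to be enhanced, so not every project service is a new location. The intervention concentrates on two of about five dusuns, and the survey dusuns were chosen before placement was known, so many respondents may live away from a project center. These points stand as limits on size and certainty. They do not make knowledge of location a measure of importance.

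A second reply is that a factual item is a sensible proxy. Pilots found social desirability bias among caregivers and difficulty with subjective questions. This is fair, and it weakens any call for new attitude items. It does not justify the label on the result.

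Third, child development is the primary objective, the pathway analysis names child development and service utilization rather than awareness, and supply is reported separately under hypothesis 1. This limits the damage to one of six hypotheses.

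A reader might go further and infer that the bias always favors the project arm and is very large. The 2004 national counts in Indonesian context total 47,696 + 1,560 + 5,169 + 1,789 = 56,214 programs. For 28 million children that is 56,214 / 28,000,000 × 300 = 0.60 per village of 300 children (5 dusuns × 60). If programs were scattered at random, exp(−0.60) = 55% of villages would have none. With 80% knowledge wherever a program exists, and a program in every project village, the result would be 80% v 0.80 × 0.45 = 36%, a gap of 44 points. The documents do not support that figure for this trial. It uses national data from years before the baseline, leaves out posyandu and midwives, and assumes the spread, the knowledge rate and universal project presence. The claim that the bias always favors the project also fails to allow for the midline overlap and for enhanced services.

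**Conclusion.** The point holds as a mismatch between hypothesis and outcome. The only test of hypothesis 5 does not measure perceived importance and can respond to added supply, so a positive finding would not support the conclusion as worded. This rests on the text alone.

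The size of any supply effect cannot be derived from the document. The 5 to 20 point gaps, with power from about 30% to above 99% at 50% knowledge, show only that the effect could matter. They assume equal knowledge in both arms, absence scored as not knowing, and invented presence rates. Exposure is greatest for Batch 1 against matched controls at endline and smaller at midline. The plan should be corrected, but the rest of the trial is not affected.

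**What to change.** In Planned analyses, relabel the outcome as awareness or visibility of available services. Either move it under hypothesis 1 or 2 or reword hypothesis 5 to match, and state that no conclusion about the importance of ECED will be drawn from it.

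Where the data allow, add a supply-neutral version: knowledge only of services that exist in the respondent's village, or only of services that exist independently of the project, such as posyandu and midwife. State which services count as key and how absence is scored.

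Test hypothesis 5 as worded only if a perceived-importance item was already collected identically in all arms. The questionnaires are said to record attendance, "but also reasons for participating (or not) in ECED services". Those reasons are a doubtful substitute, because having no service nearby is itself a reason not to attend, and the article does not show whether any answer captures importance. New items are probably no longer possible: the Discussion describes the endline survey as being designed, but Table 1 gives its actual dates as February to July 2013.

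Relabeling and limiting the conclusion need no new data. The price is that hypothesis 5 in its present wording may be left without a direct test.

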The first steps in the analysis will be to further validate the instruments used. This will be undertaken by assessing floor and ceiling effects, correlates between measurements, and investigating gradients with socio-economic indicators as well as with age and gender. These analyses will also provide a unique snapshot of the early development of a large cohort of Indonesian children [40].

Having two control groups, an experimental and a matched control, is an unusual feature of this evaluation. Usually an experimental design would be the first choice, and the entire sample would be allocated to this. This rule of thumb was not followed for this evaluation because the effect of the intervention is expected to depend on the duration of exposure to the project. The largest measurable impact is thus expected for children that live in Batch 1 villages at the end of the project. Measuring this impact is the main objective of the evaluation. The randomized control sample is of limited value in estimating this impact as it will have already received the intervention by the end of the project. The matched control sample, on the other hand, will never receive the intervention. Using the observations from the Batch 1 villages and matched control villages, the impact of the project can be estimated using:

(1)$$Y_{\mathrm{ijt}}=\alpha_{t}+X_{\mathrm{ij}0}\beta_{t}+\delta_{t}T_{j}+\epsilon_{\mathrm{ijt}}$$

Where *i* denotes the child, *j* the village, and *t* = 1,2 indicates the time of the baseline, midline and endline surveys. *X* is a vector of village and child baseline characteristics, and *T* indicates whether the village received the project (*T* = 1 for Batch 1 villages and *T* = 0 for matched control villages).

This estimate is a valid impact estimate under the assumption that the outcomes at endline, given baseline characteristics, would be equally distributed in the Batch 1 villages and matched control villages in the absence of the intervention. This assumption cannot be tested at baseline but can be tested at midline. At midline, the averages observed in the randomized control sample of Batch 3 villages are a valid estimate of the expected outcomes in Batch 1 villages in the absence of the intervention. Whether these estimates are equal to those of the matched control sample can be tested by estimating:

(2)$$Y_{\mathrm{ij}1}=\gamma +X_{\mathrm{ij}0}\theta +\mathrm{\pi M}C_{j}+\epsilon_{\mathrm{ij}}$$

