An estimate of *π* that is not significantly different indicates that the matched control sample would have been a valid control group at midline when using the sample of matched control (*MC* = 1) and randomized control villages (*MC* = 0). If this is true, it also increases the ‘comfort factor’ of making this assumption at endline. If not, it provides an indication of the direction in which the estimates from (1) will be biased.

At midline, the experimental design makes it possible to estimate the average treatment effect of the first 18 months of intervention with minimal assumptions. Batch 3 villages will still be a valid control group. Using data from Batch 1 (*T* = 1) and Batch 3 (*T* = 0), the average treatment effect can be estimated by:

(3)$$Y_{\mathrm{ij}1}=\rho +X_{\mathrm{ij}0}\varphi +\vartheta T_{j}+\epsilon_{\mathrm{ij}}$$

Outcomes will be indicators of child development and utilization of early childhood development services. The latter is of interest as the projects aims to increase child development through improved access to early childhood development services. Considering both types of outcome variables provides an opportunity to evaluate the pathways of impact.

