#### Deviations from planned design and consequences for analysis

As mentioned earlier, one deviation from the research design was that the randomized assignment to Batches 1 and 3 was not adhered to. This happened in our case for 20 out of 310 villages. Because this misallocation occurred in relatively few villages, these can be accommodated by using an instrumental variable (IV) estimator in (3). In this case, *T*_*j*_ in (3) is replaced with the actual batch, or the time period of the actual intervention at the time of the survey, and is instrumented with *T*_*j*_. A comparison between the non-instrumented estimate and the IV estimate is insightful in this case. To estimate the impact of the entire project at endline using (1), there is only the non-experimental estimator available. The deviation between the non-instrumented estimator and the IV estimate will give an indication of the effect of using a non-experimental estimator on the parameter estimate.

Another significant deviation from the research design was that the baseline data collection did not take place before the Batch 1 villages started implementing the project. The baseline data collection took place on average 6 months after Batch 1 villages started implementation. Further, the midline data collection took place an average of 9 months after Batch 3 villages started implementation. The delays were a result of the MoNE’s prolonged procurement process to engage the survey fieldwork company and a desire to dispense the funds to the communities. Given these timing issues, in order to assess the impact of the project we will construct measures of dosage, such as months the project was active in a given village.

The consequence of the late baseline survey is that the pre-intervention values cannot be observed from the baseline data for Batch 1 villages. For Batch 3 villages, the intervention had not occurred at the time of the baseline. This is particularly problematic for pre-intervention levels of outcome variables, which in equations (1), (2) and (3) would normally be included in *X*_*ij*0_. With a late baseline, these outcome variables could already have been influenced by the intervention, thus leading to correlation between *X*_*ij*0_ and *T*_*j*_, also in the experimental design.

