Our approach to manage this issue is two-fold. For the utilization variables, which we believe responded quickly to the opening of early childhood development services, we intend to reconstruct a variable of utilization before the start of the project based on retrospective data collected in the baseline survey. For child development variables, we intend to use the baseline data to estimate the impact of the intervention after 6 months comparing Batch 1 to Batch 3 villages.

The consequence of the late midline survey is more limited. When conducting the midline analysis in (3), the comparison is no longer between 18 months of implementation and no project, but rather between 20 and 9 months of implementation. This is because project implementation was delayed in Batch 3. By the time the midline data were collected, Batch 3 villages had been implementing the intervention for only 9 months. Therefore, we intend to use the midline data to estimate the impact of the project after Batch 1 villages have received the project for 20 months and Batch 3 villages have received the project for 9 months, that is, the impact of 11 months of differential exposure. For outcome variables which respond quickly to the treatment, such as utilization, this is a problem as both Batch 1 and Batch 3 villages received treatment. Our strategy will be to focus on utilization variables which capture utilization over the entire evaluation period, not only at the time of the survey. For outcome variables which respond more slowly to the treatment, such as child development outcomes, we simply report the comparison as above, indicating that this is the impact of the 18-month difference in treatment duration.

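### The midline check of the matched controls (equation 2) assumes Batch 3 is untreated, but Batch 3 was already running the project, so a null or negative π cannot be read as planned

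*Protocol article*

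**What the plan says.** All references are to the Protocol article.

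- **Planned analyses.** Full-project impact at endline is to be estimated by equation (1), Batch 1 against matched controls. It is valid if both groups would have had the same endline outcomes, given baseline characteristics, without the project. Of this condition the plan says: "This assumption cannot be tested at baseline but can be tested at midline". The reason given is that in the midline round "the averages observed in the randomized control sample of Batch 3 villages are a valid estimate of the expected outcomes in Batch 1 villages" had there been no project.
- **Planned analyses, after equation (2).** π contrasts matched controls with Batch 3. A non-significant π "indicates that the matched control sample would have been a valid control group at midline" and adds comfort about endline. Otherwise π is to show which way equation (1) is biased.
- **Deviations from planned design and consequences for analysis.** "the midline data collection took place an average of 9 months after Batch 3 villages started implementation". The next paragraphs begin "The consequence of the late midline survey is more limited". They restate equation (3) as 20 against 9 months of exposure and adapt the utilization outcomes. Equation (2) is mentioned again only for the late-baseline covariate problem. Dosage measures are announced for assessing impact, not for equation (2).
- **Same section.** "For Batch 3 villages, the intervention had not occurred at the time of the baseline".
- **Same section.** The gap between the non-instrumented and instrumental-variable (IV) estimates in equation (3) "will give an indication of the effect of using a non-experimental estimator on the parameter estimate".

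**The concern.** Equation (2) works as a validity check only if its comparator is untreated. By the plan's own account, Batch 3 was treated at midline. The interpretation rule for π was written for the intended schedule and was not revised when the schedule slipped, although equation (3) was.

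The plan names full-project impact in Batch 1 at endline as its chief aim and says that only a non-experimental estimator is available for it. Equation (2) is the main planned safeguard for that estimate. If π is read as written, sound matched controls may be judged worse off than Batch 3, or unsound ones may pass. The second check, the IV gap, cannot stand in, because matched controls do not enter equation (3).

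**Working it through.** **1. Exposure.** The plan's figures reproduce: 20 − 9 = 11 months of differential exposure. Table 1 fits the 9-month average poorly:
- Batch 3 grants ran from November 2009 to June 2010 and midline was July to August 2010. That gives about 0 to 10 months since grant; from mid-range to mid-range (1 March to 1 August 2010) is 5 months.
- Batch 3 services opened from January 2010, so at most about 8 months to the end of August 2010.

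The passages must be reconciled. On either reading, exposure is not zero.

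**2. What π estimates.** Given the covariates, let S = untreated mean of matched controls − untreated mean of Batch 3, and let τ = project effect already present in Batch 3 at midline. Then
- π = S − τ.
- Batch 1 and Batch 3 are exchangeable as randomised, so if the untreated gap persists to endline the bias of equation (1) is −S.

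Reading the cases:
- S = 0 (valid controls): expected π = −τ. The rule reads this as worse-off controls and upward bias in (1). Both are wrong.
- S = τ: expected π = 0. The rule passes the controls, yet (1) is biased downward by τ.
- π clearly above 0 with τ ≥ 0: S > 0, so downward bias in (1) is correctly signed.

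**3. Precision of π.** Inputs: ICC 0.23 and 10 children per village (Sample size calculation); 100 Batch 3 and 90 matched villages, and 20 households per village (Sampling procedures). Assumed: two-sided 5% test, normal approximation, unit SD, no covariate adjustment.

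SE(π) = √[(ICC + (1 − ICC)/m)(1/100 + 1/90)]
- m = 10: √(0.307 × 0.02111) = 0.081 SD; 95% half-width 1.96 × 0.0805 = 0.158 SD, which is 62% of the 0.255 SD effect in the sample-size text.
- m = 20: √(0.2685 × 0.02111) = 0.075 SD; half-width 0.148 SD.

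With no contamination and m = 10, a true gap of 0.10 SD is non-significant 76% of the time, and 0.15 SD 54%.

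**4. Effect of contamination when S = 0 (m = 10).** The plan gives no value of τ. The values below are assumptions scaled from its effect sizes.

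| Assumed τ (SD) | Basis | P(π significant) |
|---|---|---|
| 0.035 | 0.255 × 5/36 | 7% |
| 0.064 | 0.255 × 9/36 | 12% |
| 0.115 | 0.255 × 9/20 | 30% |
| 0.255 | full effect at once | 89% |

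The nominal rate is 5%. Nearly all of these rejections point the wrong way, to worse-off controls. If instead S = τ, the test passes 95% of the time by construction.

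**5. The IV gap.** Equation (3) uses Batch 1 and Batch 3 only. Its IV and non-IV estimates differ because 20 villages departed from their assigned batch. Matched controls were picked by district officials from villages outside the project, which is a different selection process.

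**The case against.** The strongest defence has five parts.

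- **The plan is cautious.** It says that a null π indicates validity and adds comfort, and the Discussion names internal validity as the matched group's main weakness. This stands. A reader might infer that non-significance is treated as proof, or that the IV gap is claimed to measure the bias of equation (1). The wording is softer on both.
- **π is not useless.** A reader might conclude that it can never sign the bias. That goes too far, because a clearly positive π still does so if the project effect is non-negative.
- **Slow outcomes may be little affected.** The plan separates utilization, which it believes responds quickly, from child development, which responds more slowly. At small τ the false-rejection rate is only 7% to 12%. This stands, and the distortion must be judged outcome by outcome.
- **The baseline cannot replace midline.** A reader might infer that the delays simply swapped the two rounds, so that the assumption is now testable at baseline. The assumption concerns later outcomes given baseline characteristics. A baseline comparison checks levels only.
- **Equation (2) is a diagnostic and Batch 3's exposure is disclosed.** True, and no impact estimate changes. But the disclosure is never carried into how π is to be read.

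The precision figures are also approximate: the ICC comes from junior secondary enrolment, and covariates could reduce the SE.

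**Conclusion.** The point holds in limited form. The plan contradicts itself on whether Batch 3 is untreated at midline and adapts equation (3) but not equation (2). As written, a null π does not support validity and a negative π does not sign the bias of equation (1). Only a clearly positive π keeps its meaning, and only if the project effect is non-negative.

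The existence of the distortion rests on the plan's own statements. Its size depends on τ, which is unknown, and on Batch 3's true exposure, where the text and Table 1 need reconciling. Separately, with an unadjusted SE of 0.075 to 0.081 SD, a non-significant π would be weak reassurance even against an untreated comparator.

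The documents do not support saying that both checks are worthless or that the matched controls are shown to be biased. They support saying that the stated reading of π is wrong, and that the IV gap does not inform the bias from matched controls chosen outside the project.

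**What to change.** 1. State that midline π estimates S minus Batch 3's project effect, and withdraw the rule that reads validity or bias direction directly from it. Note that the distortion is likely to differ between fast and slow outcomes.
2. Reconcile the 9-month average with the Table 1 dates.
3. Add a comparison of matched controls with Batch 3 on baseline data, without baseline outcomes as covariates. Say how villages that departed from their assigned batch are handled, since any Batch 3 village that started early was already exposed, and matched controls were re-selected when Batch 1 villages changed. Run a sensitivity analysis without Sarolangun, which was re-surveyed from October to December 2009 when Batch 3 grants had begun.
4. Report π with its confidence interval, and present the baseline result as a check of levels, not of later trends.
5. Do not subtract the baseline gap from endline estimates that already adjust for or difference out baseline outcomes, because that risks correcting twice.
6. State that the IV versus non-IV gap in equation (3) reflects selection among switched project villages and does not inform the bias from the matched controls.

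The cost is revised analysis wording and one further analysis of data in hand. No new data collection is needed.
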